### Study modifications during COVID-19 pandemic

2.7

Given challenges associated with in-person research due to the COVID-19 pandemic, the PIs made approved study modifications that allowed for continuance of the trial. Specifically, we modified T3 to include remote strategies both in terms of the stressor and strategy for measuring heart rate variability (HRV). This included switching from our original stressor, the Trier Social Stress Test [49] to Cyberball [48], which is a virtual ball-toss game that can be used for research on ostracism, social exclusion, or rejection. During Cyberball, the participant is told that they are playing a computerized ball tossing game with three other players over the internet: in reality, the other ‘players’ characters are controlled by the computer. After a few initial trials where the other players toss the ball to the participant, the other players then exclude the participant, only throwing to one another. This exclusionary experience has been found to be distressing to participants [50].

For HRV measurement, we will use the Firstbeat Bodyguard 2 (BG2) [51]. BG2 is a beat-to-beat heart rate monitoring device that is intended for short-term or long-term monitoring of heart rate variability and physical activity. The device records ECG with electrodes, processes the signal with an integrated algorithm and provides beat-to-beat R-to-R interval as an output with 1 ms resolution. The device easily attaches directly to the skin with two chest electrodes and starts recording data automatically. The BG2 has been designed for 24 h recordings. R-to-R timing data is downloaded from the BG2 to a computer for further analysis using standard HRV analysis software.

### Data analysis

2.8

All analyses will use a two-sided test of hypotheses, with a significance level of 0.05 unless otherwise noted, and will be run in SAS v9.4 or higher, R v4.1.1 or higher, or QIIME2 2019.1 or higher. Group profile variables will be summarized as means and standard deviations (SD), medians and ranges, or *N* and percent and will be compared between those allocated to LGG supplementation and those allocated to placebo supplementation using *t*-tests, Wilcoxon rank-sum tests, chi-square tests and Fisher's exact tests, as appropriate. Group profile variables that are found to be significant at the *p* < 0.10 level and are considered as plausible potential confounders will be included as noted in the analysis plans below, although given randomization, the number meeting this criterion will be low. These may include demographics, history of TBI, childhood trauma, chronic health conditions, diet, beverage consumption, medications, BMI, insomnia severity, sleep duration and quality, and/or exercise. Data from the Test of Memory and Malingering (TOMM) [52,53] will be used to increase understanding regarding participants' ability to engage in mIGT testing. mIGT scores will not be used from those whose TOMM scores suggest poor effort/engagement.

The recruitment goal for this study is 59 participants per group. Anticipating a 15% attrition rate, we will have 50 participants per group for the final analysis. For the primary outcome of plasma concentration of CRP inflammatory biomarker, linear regression will be used to model the changes between T2 and T3, as a function of group, sex, the baseline value of CRP and any potential confounders identified as noted above. A similar analysis will be performed for the exploratory clinical outcome of PTSD symptoms (PCL-5 score). For the gut microbiome, linear regression will be used to model the changes between T2 and T3 both in alpha diversity, measured by Shannon Diversity Index, and in the gut microbiota community, quantified by Unweighted and Weighted UniFrac [54], pairwise distance between times for each individual, as a function of group, sex, the baseline value of the outcome, and potential confounders. Linear regression will also be used to model changes between T2 and T3 in IP (fatty acid binding protein 2 [FABP2], D-amino acid oxidase [DAO]), as well as plasma biomarkers of inflammation (IL-6, IL-10, IFNγ, IL-1α, IL-1β, IL-12p70, IL-8, and IL-4), and decision making as a function of group, sex, the baseline value of the outcome, and potential confounders. For stress outcomes from Cyberball (HRV, visual analog scale [VAS] and psychological stress measure [PSM]), linear regression will be used to model each outcome at T3 as a function of group. For each outcome measured at T2 and T3, the estimated mean difference in change between the groups will be reported with 95% confidence intervals (CI). For the stress outcomes measured only at T3 the estimated mean differences between the groups at T3 will be reported with 95% CIs. For the mediation analysis, we will use methods proposed by VanderWeele et al. for multiple mediators [55,56], examining whether the relationships between probiotic treatment and the outcome measures (PTSD symptoms, stress response, decision making) are mediated by changes in the gut microbiome, IP, and inflammation.

Assuming a CRP standard deviation of 1.19 mg/L as observed in Brenner et al. [40], 50 participants per group provides 85% power to detect a difference in change between groups of 0.73 mg/L at the α = 0.05 level for the primary outcome.

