**Fig. 2 fig2:**
[figure not shown]
Consort diagram. Abbreviations: LGG, *Lactobacillus rhamnosus* GG.

At Time 1 (T1, Initial Study Assessment), diagnoses of PTSD and functional bowel disorder (FBD) will be confirmed. A blood draw will be conducted to identify an individual's baseline CRP level for inclusion, based on plasma CRP concentration >1.0 mg/L, the clinical threshold for average risk of cardiovascular disease [46]. Between Time 1 and Time 2 (T2, Assessment and Randomization Visit), participants will keep a pre-supplementation daily diary of gastrointestinal (GI) symptoms for approximately 2 weeks. At T2, data will bei collected regarding group profile/potential confounding variable measures, psychological outcomes, and biological signatures. Between T2 and Time 3 (T3, End of Study Period Assessment), individuals will supplement with LGG or placebo (for 8±2 weeks), and measures of tolerability, safety, acceptability, and feasibility will be collected. Data regarding diet, sleep, exercise, and PTSD symptoms will also be collected (via phone or email surveys). At T3, data will be collected regarding psychological outcomes (e.g., PTSD symptoms), and biological signatures (e.g., inflammation), as well as potential covariates (see Fig. 3, Participant Flow Diagram).

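### Covariates enter the primary CRP model through a between-arm imbalance test at p < 0.10, so the model is not fixed in advance and covariates are picked by chance imbalance rather than prognosis

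*Protocol article*

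**What the plan says.** Section 2.8 (Data analysis) says that group profile variables "will be compared between those allocated to LGG supplementation and those allocated to placebo supplementation" using t, Wilcoxon, chi-square or Fisher tests. Two conditions then admit a variable to the models: "Group profile variables that are found to be significant at the *p* < 0.10 level and are considered as plausible potential confounders". The candidate list is open-ended: "These may include demographics, history of TBI, childhood trauma, chronic health conditions, diet, beverage consumption, medications, BMI, insomnia severity, sleep duration and quality, and/or exercise". The authors expect few to qualify: "although given randomization, the number meeting this criterion will be low".

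The next paragraph carries the selected variables into the primary analysis, a linear regression of the T2-to-T3 change in CRP "as a function of group, sex, the baseline value of CRP and any potential confounders identified as noted above". Group, sex and baseline CRP are therefore fixed, and the remaining terms depend on the data. The same allowance for potential confounders recurs in the models for PCL-5, the gut microbiome, intestinal permeability, the cytokines and decision-making.

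**The concern.** Allocation is random, so any baseline difference between the arms arises by chance. A small p-value for imbalance shows that a chance event occurred. It does not show that the variable is related to the change in CRP, which is what decides whether adjusting for it helps. The rule can therefore pass over a strong predictor that happens to be balanced and admit a weak one that happens not to be.

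Two things are at stake. First, the model behind the trial's single primary result cannot be written down until the arms have been compared. Second, adjustment could buy precision at almost no cost, and this rule largely gives that up. The rule is stated in the article itself, so this is not a detail merely left to an unseen analysis plan.

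**Working it through.** **Inputs from the article (section 2.8):** 50 per group analysed, SD 1.19 mg/L, difference 0.73 mg/L, two-sided alpha 0.05, stated power 85%, selection threshold p < 0.10, 11 candidate headings (counting sleep duration and quality as one).

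**Assumptions, not in the article:** candidates are independent and normally distributed; 1.19 is the SD left after sex and baseline CRP; the extra covariates explain a share R² of that remaining variance, varied from 0 to 0.30. The plausibility judgement is not modelled.

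**1. The plan's own power figure.** SE = 1.19 × √(2/50) = 0.238. Then 0.73/0.238 = 3.067, and Φ(3.067 − 1.960) = Φ(1.107) = 86.6%. The noncentral t with 98 df gives 85.9%. The stated 85% is reproduced, and it does not rely on covariate adjustment.

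**2. How often the model changes.** Expected number flagged = 11 × 0.10 = 1.1. Chance of at least one = 1 − 0.9^11 = 1 − 0.314 = 69%. The same formula gives 41% for 5 candidates, 72% for 12 and 88% for 20. The plausibility condition can only lower these figures.

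**3. What naming covariates in advance could give.** The SE shrinks by √(1 − R²), so power = Φ(3.067/√(1 − R²) − 1.960):

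- R² = 0.10: Φ(1.273) = 89.9%
- R² = 0.20: Φ(1.469) = 92.9%
- R² = 0.30: Φ(1.706) = 95.6%

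**4. What the rule does.** Simulation with 12 candidates (sleep duration and quality split), 8,000 trials per setting, 50 per arm, SD 1.19. Power is at a difference of 0.73; the last two columns are for the p < 0.10 rule under no effect.

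| Candidates | Power, no extra covariates | Power, p < 0.10 rule | Power, named in advance | Null rejection, rule | Mean model SE / empirical SD, rule |
|---|---|---|---|---|---|
| None prognostic | 86.1% | 84.0% | 85.9% | 5.0% | 0.2437/0.2444 = 1.00 |
| 3 prognostic, R² = 0.20 | 86.2% | 86.0% | 91.9% | 4.0% | 0.2417/0.2323 = 1.04 |
| 3 prognostic, R² = 0.30 | 86.0% | 86.4% | 94.5% | 4.0% | 0.2405/0.2286 = 1.05 |
| 12 prognostic, R² = 0.30 | 86.6% | 86.8% | 92.3% | 3.8% | 0.2403/0.2270 = 1.06 |

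Separate runs with 11 candidates agree. At R² = 0.10, 0.20 and 0.30, one gave power of about 86%, 85% and 86% under the rule, 86% with no extra covariates, and 89%, 92% and 95% with covariates named in advance. Its null rejection under the rule was 3.8% to 4.8%. Across the 11-candidate runs, the excess of the model SE over the true sampling error at R² = 0.30 was about 5% to 7%; the largest, in SD units, was 0.2015/0.1884 = 1.07.

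**5. Width against the model without extra covariates.** In the null runs the rule's mean SE is 0.2437 against 0.2372 (+2.7%) with no prognostic candidates, 0.2417 against 0.2376 (+1.7%) at R² = 0.20, and 0.2405 against 0.2378 (+1.1%) at R² = 0.30 with three prognostic candidates. The rule widens the reported interval only slightly against that model. The larger gap is against covariates named in advance.

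**The case against.** The strongest defence is that the procedure errs on the safe side. Sex, the stratification factor, and baseline CRP are already in the model whatever the tests show. Power under the rule stays close to the planned 85%. The forgone gain rests on an R² that the article does not give, and baseline CRP may already take most of the explainable variance. All of this stands. It limits the size of the point, but it does not make imbalance testing a sound way to choose covariates.

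Four stronger readings are tempting, and the article does not support them.

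- **That the rule inflates false positives.** Applied mechanically it does not. If someone who could see outcomes kept whichever flagged subset gave the smallest p-value, simulated type I error would be about 6.0% to 6.3%. The article does not say that the plausibility judgement is made that way, the trial is double-blind, and who judges and when may be set out in an analysis plan that is not shown.
- **That values measured after randomisation may enter the model.** The text under Figure 2 in section 2.1 does list for T3 "biological signatures (e.g., inflammation), as well as potential covariates". But the same paragraph places the group profile and potential confounder measures at T2, the randomisation visit, and section 2.8 selects only from group profile variables.
- **That the authors are wrong to expect few selections.** An average of 1.1 out of 11 is low, and the plausibility condition lowers it further. Few selections are still enough to change the model in most trials.
- **That the error bars are materially wider.** Against a model without extra covariates the widening is only about 1% to 3%. The 5% to 7% figure compares the reported SE with the true sampling error when candidates are prognostic, which means the interval is conservative.

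**Conclusion.** The point holds in a limited form. The article fixes a selection rule for the primary model that responds to chance imbalance instead of association with CRP, and so leaves that model undetermined until the arms are compared. If all 11 headings were independent candidates, about 69% of trials would flag at least one before the plausibility judgement. The consequence is mildly conservative inference (null rejection about 3.8% to 5.0%) and forgone precision: power of about 85% to 86%, against 89% to 95% with covariates named in advance that explain an assumed 10% to 30% of the variance left after sex and baseline CRP. If the candidates predict nothing, there is no gain to forgo, and the rule costs about two points of power (86.1% to 84.0%).

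The 85% power statement is correct and is not in question. This should be fixed because it governs the single primary analysis and the remedy is cheap. It is not a defect that invalidates the trial.

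**What to change.** Delete the p < 0.10 selection rule for the efficacy models. Before unblinding, write the primary model as group, sex, T2 CRP and, if wanted, a short named list of T1 or T2 covariates chosen on prior prognostic grounds from data already collected. BMI and age are examples of what is available; the article gives no evidence of how strongly either predicts CRP, so the team should justify its choice. Report any adjustment prompted by observed imbalance only as a labelled sensitivity analysis. Use the same approach in the exploratory models that carry the potential-confounder clause.

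The cost is wording, plus one or two degrees of freedom for the named covariates. No new data are needed and the sample size does not change.

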**Inclusion criteria**
History of at least one deployment in support of Operation Enduring Freedom/Operation Iraqi Freedom/Operation New Dawn (OEF/OIF/OND)
Current diagnosis of PTSD per the Clinician Administered PTSD Scale-5 (CAPS-5)
Current diagnosis of a Functional Bowel Disorder including Irritable Bowel Syndrome [IBS]) by the ROME IV
CRP level of 1.0 mg/L or above at Time 1
Medical clearance to participate by study providers
Age between 18 and 60
Ability to provide informed consent
Willingness to abstain from probiotic supplements (pills, tablets, oils, foods, etc.) other than the investigational product provided until all study procedures are completed
Willingness to provide blood and stool samples

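### Prespecifying the T1 screening CRP beside the T2 CRP as a covariate would probably sharpen the primary analysis, for one degree of freedom

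*Protocol article*

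**What the plan says.** The protocol article provides for two CRP measurements before treatment starts.

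- **T1.** Section 2.1: "A blood draw will be conducted to identify an individual's baseline CRP level for inclusion". Table 1 makes the result an eligibility condition: "CRP level of 1.0 mg/L or above at Time 1".
- **T2, the randomisation visit.** Data are "collected regarding group profile/potential confounding variable measures, psychological outcomes, and biological signatures". Between T1 and T2, "participants will keep a pre-supplementation daily diary of gastrointestinal (GI) symptoms for approximately 2 weeks", so the two draws are about two weeks apart.

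T3 follows T2 by 8±2 weeks. For the primary outcome, section 2.8 states that "linear regression will be used to model the changes between T2 and T3, as a function of group", and the remaining terms are "sex, the baseline value of CRP and any potential confounders identified as noted above". The visit that supplies this baseline value is not named. The potential confounders are group profile variables that differ between arms at p < 0.10; the examples listed there do not include T1 CRP.

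The power statement in section 2.8 assumes an SD of 1.19 mg/L and 50 analysed per group, and gives 85% power for a difference in change of 0.73 mg/L at a two-sided 0.05 level.

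**The concern.** A second reading of the outcome variable, taken before randomisation, is often a good predictor of the final reading. If CRP fluctuates within a person from visit to visit, one value at T2 measures that person's usual level imperfectly, and T1 carries extra information about it. The plan collects T1 CRP in everyone it randomises and then makes no use of it in the primary model. The only route by which it might enter is the screen for chance imbalance, and that is the wrong test: the precision gained from a covariate depends on how well it predicts the outcome, not on whether the arms happen to differ on it.

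At stake is some precision in the single primary comparison. Validity is not at stake.

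**Working it through.** **1. The plan's own figure.** The standard error is 1.19 × √(2/50) = 0.238 mg/L, and 0.73/0.238 = 3.07. Normal-approximation power is Φ(3.07 − 1.96) = 86.6%. The noncentral t with 98 degrees of freedom gives 85.9%. Both are close to the stated 85%. For 85% power the normal formula needs 48 per group, and 50/0.85 = 58.8 gives 59 randomised per group. The stated figures reproduce.

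**2. Inputs not in the documents (assumptions).** The correlations r₁₂, r₂₃ and r₁₃ between the CRP values at T1, T2 and T3 are not given. I take equal variances and r₁₂ = r₂₃ = r from 0.3 to 0.8, and vary r₁₃. The documents do not say what kind of SD 1.19 mg/L is. The main calculation takes it as the residual SD of the T2-adjusted model, with 96 residual degrees of freedom (100 less intercept, group, sex and T2 CRP).

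**3. Formula.** Once T2 is in the model, T3 − T2 and T3 have the same residual variance. Adding T1 multiplies that variance by 1 − ρ², where ρ is the partial correlation of T1 with T3 given T2:

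ρ = (r₁₃ − r₁₂r₂₃) / √[(1 − r₁₂²)(1 − r₂₃²)]

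With all correlations equal, ρ = r/(1 + r) and the ratio is (1 + 2r)/(1 + r)². At r = 0.5 this is 2/2.25 = 0.889. If r₁₃ = r₁₂r₂₃, so that T1 informs T3 only through T2 (AR(1)), then ρ = 0 and the ratio is 1.

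**4. Results, T1 and T2 against T2 alone** (power for 0.73 mg/L, 50 per group, starting from 85.9%):

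| Assumed r₁₃ | r | Variance ratio | Power |
|---|---|---|---|
| equal to r | 0.3 | 0.947 | 87.7% |
| equal to r | 0.5 | 0.889 | 89.6% |
| equal to r | 0.7 | 0.830 | 91.5% |
| equal to r | 0.8 | 0.802 | 92.4% |
| midway between r and r² | 0.3 to 0.8 | 0.987 to 0.951 | 86.4 to 87.6% |
| r² (AR(1)) | 0.3 to 0.8 | 1.000 | 85.9% |

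**5. Selection on T1.** Entry at 1.0 mg/L or above restricts the range of T1 and weakens it as a predictor. Simulated log-normal CRP with equal correlations of 0.5 to 0.8, truncated at T1 ≥ 1.0 mg/L, gave ratios of 0.84 to 0.95 and power of about 87.5 to 91.3%. Results were similar on the raw and log scales.

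**6. Other meanings of 1.19.** The variance ratios do not depend on this. If 1.19 mg/L is the SD of the unadjusted change, power in the T2-adjusted model is already 96.5% at r = 0.3 and 89.3% at r = 0.8. Under equal correlations, T1 raises these to 97.2% and 94.7%.

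**7. Cost if T1 is useless.** Going from 96 to 95 degrees of freedom changes power by less than 0.01 percentage point. The expected variance rises by 96/95 = 1.011, about 1%.

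**The case against.** The strongest reply is that nothing here is wrong. Adjusting a change from T2 for the T2 value is standard analysis of covariance, and leaving out a second pre-randomisation value is not an error. The size of the benefit rests on correlations that the documents do not give. T1 and T3 are about 10 weeks apart and T1 and T2 about 2, so equal correlations are the favourable case, and the gain may be nil. All of this stands, and it limits the point to a recommended refinement. It does not remove it: the covariates are set out in the article, T1 is already collected, and the possible loss is far smaller than the plausible gain.

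A reader might also infer that the model adjusts for T1 alone, because section 2.1 calls the T1 draw baseline. Under equal correlations of 0.8 down to 0.3, that would multiply the residual variance by 1.11 to 1.54 relative to T2 adjustment and cut power to 82.1 to 68.7%. The documents do not support this reading. Section 2.1 ties the word to inclusion. Section 2.8 puts the covariate in the same sentence as the change from T2, and it describes results for outcomes measured at T2 and T3. Naming the visit is a detail that an article can leave to the analysis plan.

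**Conclusion.** The point holds as a cheap improvement to a valid primary model. Under equal correlations of 0.3 to 0.8, adding T1 CRP to T2 CRP would reduce the residual variance by about 5 to 20%. With selection at entry and correlations of 0.5 to 0.8, the reduction is about 5 to 16%. In power this is 0 to about 6.5 percentage points above 85.9%, with zero reached under AR(1). A gain is likely if visit-to-visit variation in CRP is largely noise around a stable personal level, but that is an assumption.

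Both CRP values precede randomisation, so the estimand and the type I error are unchanged. It would be too strong to say that the trial is underpowered or that the extra precision is assured. A move to a log scale is a separate question: it would change the effect from a difference in mg/L to a ratio, which the power statement does not cover.

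**What to change.** In section 2.8, write the primary model as the change in CRP from T2 to T3 on group, sex, CRP at T2 (the baseline of the change) and CRP at T1, plus whatever confounder terms the plan retains. Put both CRP covariates on the scale used for the primary CRP analysis. In section 2.1, call the T1 value screening CRP, so that baseline refers only to T2. Make the change before unblinding.

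The cost is one model term, one change of wording and one degree of freedom. No visit, blood draw or participant is added, and no one drops out of the analysis for want of a T1 value, because eligibility requires it. If T1 came from a different assay it would still be a valid covariate. The sample size and power statement can stay as they are.

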**Fig. 1 fig1:**
[figure not shown]
Working model of PTSD with an emphasis on immunomodulatory factors in the etiology and pathophysiology of PTSD. The model includes the influence of pre-existing factors that contribute to individual variability in physiological and psychological responses to trauma, leading to development and persistence of PTSD in a subset of individuals. Abbreviations: ANS, autonomic nervous system; HPA, hypothalamic-pituitary-adrenal; PTSD, posttraumatic stress disorder.

The goal of this Phase IIa placebo-controlled randomized controlled trial (ClinicalTrials.gov Identifier: NCT04150380) is to investigate the effects of daily oral administration of LGG (ATCC 53103) in a cohort of OEF/OIF/OND Veterans with PTSD as assessed by the gold standard Clinician Administered PTSD Scale-5 (CAPS-5) [44] who also have Functional Bowel Disorders (FBD), including irritable bowel syndrome. Outcomes include plasma concentration of high-sensitivity CRP (mechanistic, primary), and PTSD symptom severity (clinical, exploratory) [45]. Additional biological signatures will be considered exploratory. The primary hypothesis is that those who receive LGG supplementation will respond with lower plasma levels of CRP as compared to those allocated to a placebo supplement. Exploratory hypotheses include, as compared to those allocated to placebo, those who receive LGG supplementation will respond with: 1) decreased PTSD symptoms; 2) increased abundance of LGG and community-level shifts (e.g., increased alpha diversity) in the gut microbiota (measured using RT-qPCR and DNA sequencing of the 16S rRNA gene, respectively), decreases in IP (decreased fatty acid binding protein 2 [FABP2] and D-amino acid oxidase [DAO]), increases in plasma concentrations of anti-inflammatory biomarkers (IL-10, IL-4), decreases in additional plasma biomarkers of inflammation (IL-6, IL-8, IFNγ, IL-1α, IL-1β, and IL-12p70), reduced stress responsivity (biological and psychological) during and after participation in the Cyberball task, and improved decision-making (measured by performance on the modified Iowa Gambling Test [mIGT]); and, 3) the effect of LGG supplementation on stress responsivity, decision-making, and PTSD symptom severity will be mediated by effects of LGG supplementation on the gut microbiota, IP, and plasma biomarkers of inflammation.

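### The Shannon and UniFrac outcomes, and the microbiome mediator, do not separate the administered LGG from the rest of the gut community

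*Protocol article*

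**What the plan says.** The Introduction predicts "increased abundance of LGG and community-level shifts (e.g., increased alpha diversity) in the gut microbiota". It assigns RT-qPCR to the first item and 16S sequencing to the second. Section 2.5 repeats both within exploratory outcome 2.

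Section 2.1 places dosing between T2 and T3: "individuals will supplement with LGG or placebo (for 8±2 weeks". Section 2.2 gives one capsule daily at 1.0 x 10^10 CFU. No washout before the T3 assessment is stated.

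Section 2.8 models T2 to T3 change: "model the changes between T2 and T3 both in alpha diversity, measured by Shannon Diversity Index, and in the gut microbiota community". The community part is the within-person distance between the two visits, by unweighted and weighted UniFrac. The same section asks whether effects on PTSD symptoms, stress response and decision making "are mediated by changes in the gut microbiome, IP, and inflammation". It does not say whether 16S reads assigned to LGG stay in these metrics.

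**The concern.** The two hypotheses ask different things: whether the organism arrived, and whether the community changed. A metric computed on all 16S features answers a mixture of the two. LGG reads that appear at T3 can add branch length to unweighted UniFrac, abundance difference to weighted UniFrac, and one more feature to Shannon, even if no other bacterium has changed.

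Two conclusions depend on this. A group difference in UniFrac or Shannon could be reported as a community shift when part of it is the capsule's content. In the mediation analysis, a microbiome variable that contains the capsule's reads is partly a marker of allocation and adherence, which blurs what a mediated effect would mean.

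**Working it through.** **The plan's own figure.** The only power figure concerns CRP. The plan states "Assuming a CRP standard deviation of 1.19 mg/L" and "50 participants per group provides 85% power to detect a difference in change between groups of 0.73 mg/L", two-sided at 0.05. Normal approximation: 0.73/1.19 = 0.613 SD; 0.613 x √(50/2) = 3.07; 3.07 − 1.96 = 1.11, so power is 86.6% (85.9% by the noncentral t with 98 df). Then 50/0.85 = 58.8, that is 59, which matches "The recruitment goal for this study is 59 participants per group". The figure reproduces. It gives the 50 per group used below, which have 80% power for 0.56 SD.

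**Inputs not in the documents.** LGG's read share at T3 (p), the resident Shannon index (H), the SDs of the microbiome outcomes and the tree structure are all assumed and shown as ranges.

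**Shannon.** If the residents are unchanged and previously absent LGG enters at read share p, the change is h(p) − pH, where h(p) = −p ln p − (1−p) ln(1−p). At H = 3.5 nats:

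| p | Change (nats) |
|---|---|
| 0.01% | +0.0007 |
| 0.1% | +0.004 |
| 1% | 0.056 − 0.035 = +0.021 |
| 5% | 0.199 − 0.175 = +0.024 |
| 10% | 0.325 − 0.350 = −0.025 |
| 20% | 0.500 − 0.700 = −0.20 |

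The sign reverses at p = 20%, 7.9% and 3.0% for H = 2.5, 3.5 and 4.5. With an SD of change of 0.2 to 0.6 nats and H from 2.5 to 4.5, the chance of a significant result from the product alone is:
- 5.0 to 5.2% at p up to 0.1%;
- 5 to 12% at 1%;
- 5 to 45% at 5%;
- from 5% (H = 2.5, shift about zero) to over 90% (H = 4.5) at 20%.

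**UniFrac.** The same T2 and T3 communities were simulated with and without LGG reads: 10 random trees, 300 resident features with about half present per person, 20,000 reads, and two levels of within-person variation (log-scale SD 0.3 and 0.7). Shifts are in placebo-arm SDs. Rejection at 50 per group is Φ(5δ − 1.96) + Φ(−5δ − 1.96), where δ is the shift in SD and 5 = √(50/2).

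| p | Unweighted, LGG new at T3 | Unweighted, LGG already at T2 | Weighted |
|---|---|---|---|
| 0.01% | 0.05–0.09 | 0.01–0.02 | 0.00 |
| 0.1% | 0.06–0.10 | 0.00 | 0.00 |
| 1% | 0.07–0.10 | 0.00–0.01 | 0.00–0.06 |
| 5% | 0.08–0.12 | 0.02 | 0.07–0.42 |

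Rejection is 6 to 9% for newly detected LGG under unweighted UniFrac, almost regardless of p. For weighted UniFrac it is 5 to 6% at p = 1% and 6 to 56% at 5%. The standardised shift grows as natural within-person variation falls, so these figures rest on that variation not being close to zero.

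**Cross-check in closed form.** A branch b found only at T3 raises unweighted UniFrac by b(1−d)/(T+b), where T is total branch length and d the distance without LGG. With b/T = 1% and d = 0.30 to 0.45, the rise is 0.0069 to 0.0054. At SD 0.06 that is 0.12 to 0.09 SD and 7 to 9% rejection, in line with the simulation.

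**The case against.** A reader might infer that the LGG arm must move on these metrics by construction, in one arm only, in the hypothesised direction, and with false-positive rates up to 40%. The documents support none of these.

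- **By construction.** The effect needs LGG to be detected by 16S at T3 and, for unweighted UniFrac, undetected at T2. Neither is established. The Introduction says the strain is found in the human gut. Table 1 excludes only consistent recent probiotic use, so lighter users may carry matching features at T2.
- **One arm only.** Participants agree to abstain from other probiotics. Placebo participants who lose such features would also gain distance.
- **Direction.** The one directional community hypothesis is higher alpha diversity, and LGG lowers Shannon above the crossover.
- **Size.** The 40% figure needs b/T = 2%, d = 0.30, SD 0.04 and new detection in the whole arm: 0.02 x 0.70/1.02 = 0.0137, or 0.34 SD. If only half newly detect LGG, this becomes 0.17 SD and about 14%.

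Two broader objections also carry weight. First, read filtering is a pipeline detail that the full protocol or SAP may already settle, and no section says that LGG is to count as a community shift. Second, LGG's presence at T3 is a genuine effect of randomised supplementation and arguably part of the hypothesised path, so a filtered metric is a different estimand and not the correction of an error. This second argument stands against making the filtered version the only analysis. It does not remove the ambiguity: the article names the metrics, the model and the mediator, and following it as written cannot tell its second hypothesis from its first.

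**Conclusion.** The point holds as a cheap improvement to exploratory outcomes. As written, a group difference in Shannon or UniFrac, or a mediated effect through them, could partly reflect the administered organism.

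The likely distortion is modest. The unweighted UniFrac shift when LGG is newly detected is small beside the 0.56 SD that 50 per group can detect with 80% power. The other two metrics matter only if LGG is several percent of reads. These sizes rest wholly on the assumed read share, diversity, SDs and tree structure. The CRP analysis and its power are untouched.

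**What to change.** In section 2.8, state that Shannon, both UniFrac distances and the microbiome mediators will be computed twice: on all 16S features, and after removing the features that match *L. rhamnosus*. Apply the removal in both arms and at both visits, before any rarefaction. Filtering after rarefaction would lower the remaining depth mainly in the LGG arm and could itself bias presence/absence distances. Claim a community shift beyond the product only if it holds in the filtered version. Keep LGG abundance as its own RT-qPCR outcome. If the full protocol or SAP already sets a rule, one sentence pointing to it is enough. Settling this before unblinding avoids a post hoc choice.

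The cost is one filter step, a sentence or two of text, and one extra set of exploratory results. Because 16S cannot fully separate LGG from close native lactobacilli, a small native *L. rhamnosus* fraction is removed too, under the same rule in both arms.
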